##### Urine

Spot-urine samples will be collected at baseline and week 8 visits for patients (see **Table 2**) in 2-ml Eppendorf tubes and will be stored at −20°C for later single-batch analysis. Apart from pregnancy and drug-screening (see *Baseline Assessments Before Treatment*), all urine samples will be analyzed for 8-oxodG and 8-oxoGuo markers for systemic DNA/RNA damage with ultra-performance liquid chromatography with tandem mass spectrometry and normalized to urinary creatinine (112).

### Statistical Analyses

#### Evaluating Associations Between Baseline Measures, Changes From Baseline Measures, and Clinical Outcomes

Baseline data from each modality of interest, i.e., PET, EEG, fMRI, MRI, cognitive measures, peripheral molecular markers, and clinical/demographic patient profiles, will be available for evaluating associations with the clinical outcomes for the entire group (n = 100 included). Changes from baseline data will be available for the subgroup (around n = 40 invited), who will be re-examined with brain scans and EEG for evaluating an association between changed measures and clinical outcomes. Similarly, cognitive follow-up data will be collected for all patients after 12 weeks of treatment. Primary analyses will test mean differences in baseline measures of the biomarkers from each modality between healthy controls and patients as well as response groups (remitter vs. non-responder at week 8, i.e., primary clinical outcome) using multiple linear regressions. This analysis focuses on the two extreme outcome groups. Secondary analyses will test the association between baseline measures of the biomarkers from each modality and antidepressant treatment response on a continuous scale, i.e., relative change in HAMD_6_, using linear multiple regression. This analysis incorporates the full spectrum of clinical outcomes. Similar analyses will be performed to study the association between the change from baseline measures of the biomarkers and the clinical outcomes. Regression models will be adjusted for age and sex, as well as modality-specific relevant covariates. For instance, 5-HTTLPR status is predictive of 5-HT_4_R binding (70) and will be adjusted for in the analyses concerning 5-HT_4_R. When relevant, interactions will be evaluated, e.g., we will test if the association between the clinical outcome and 5-HT_4_R is moderated by inflammatory status. Diagnostic regression tools will be used to assess model’s assumptions (e.g., linearity of the effects, normality assumption for residuals). When violated, corrective procedures will be used (e.g., splines and bootstrap resampling) (113). As appropriate, adjustments for multiple comparisons will be performed within each modality. In the analysis of the PET data, we will instead use a Latent Variable Model relating the 5-HT_4_R binding in several brain regions (neocortex, caudate nucleus, putamen and hippocampus) to treatment outcome *via* a latent variable (114). This allows us to assess the association between 5-HT_4_R binding and clinical outcome with a single test. Patients are considered with un-verified compliance if they have taken less than 2/3 of their antidepressant medicine, missed their week 8 visit, or have undetectable serum drug levels at week 8 (i.e., <10 nM for escitalopram and <15 nM for duloxetine). Patients with un-verified compliance will not be included in primary longitudinal analyses of treatment response. Missing data will therefore be handled using complete case analysis which in regression models is valid when the probability of dropping out of the study is, conditional on the covariates, independent of the outcome. If any participants were to be excluded during the study because of their clinical outcome, a sensitivity analysis will be performed.

#### Evaluation of the Predictive Value of the Biomarkers Within Modality

Logistic regression models for the primary clinical outcome will be used to obtain the probability of each patient to be a remitter (vs. a non-responder) based on its clinical data and the value of a modality-specific biomarker. Given a threshold (e.g., 0.5), patients with an estimated probability greater than the threshold will be predicted to be remitters, otherwise to be non-responders. The receiver operating characteristic (ROC) curve will be used to assess the compromise between sensitivity and specificity of this classification across thresholds. Since a 33% remission rate is expected in treatment regimen comparable to ours (5), we will focus on the ROC curve with high-specificity. The AUC (area under the curve) of the relevant part of the ROC curve will be reported as a summary of the predictive performance of each biomarker. The classification performance (accuracy, positive predictive value, negative predictive value) at the threshold optimizing the sum specificity and specificity will also be reported. To limit optimistic biases, these measures will be estimated using five-fold cross-validation (115). A permutation procedure will be used to obtain the null distribution of the predictive performance, against which the observed performance will be compared. Additional classification schemes may be considered (e.g., responder status as defined by ≥50% reduction in HAMD_6_ at week 8), with appropriate adjustment for inflated type-I error, to facilitate comparison of the current data with other relevant clinical trials. The predictor performance will be evaluated in a modality specific fashion and at a next stage, combined predictors will be evaluated.

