## Materials and Methods

**Figure 1** shows a flowchart of the scheduled data collection over the 12 weeks of pharmacological drug treatment of patients with MDD. Healthy controls (HC) will be recruited as specified below. Patients will be examined before (at baseline; week 0) and after 1, 2, 4, 8 and 12 weeks of SSRI treatment has been initiated. Depression-severity will be monitored by the Hamilton Depression Rating scale 17 items (HAMD_17_) and its subscale of 6 items (HAMD_6_) (69). A subset of patients will be offered re-examination with PET, fMRI, and EEG after 8 weeks of treatment, to assess changes from baseline and its association to treatment response. Patients from the whole spectrum of treatment responses (from poor to excellent) will be invited in a continuous fashion for this part of the study until allotted re-examinations are completed. All patients will also repeat cognitive testing at week 12. The power analysis in preparation of the study was primarily anchored to the PET modality. We estimated that we needed to include 100 patients to reach a statistical power of 80% to detect an association between treatment response (binary classification, i.e., remitters vs non-responders, see response-definition below) and baseline 5-HT_4_R non-displaceable binding potential (BP_ND_). These calculations were based on an expected 20% maximum drop-out, ~50% remission rate after 8 weeks of treatment (5, 6) and an expected difference of 8% in 5-HT_4_R binding between remitters and non-responders, corresponding to the previously found effect sizes on 5-HT_4_R change in BP_ND_ after fluoxetine treatment (18). Calculations were further based on an average BP_ND_ of 0.71 and a standard deviation of 0.073 (18, 70). With a rescan subgroup of approximately 40 patients, and a Gaussian distribution of change in BP_ND_ with an SD of 0.08 (log scale), we had an expected power of 80% to identify a significant association between longitudinal changes in BP_ND_ and changes in HAMD_6_ (i.e., secondary clinical outcome, continuous scale).

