#### Predictive Value of the Biomarkers Across Modalities

Two strategies will be considered to optimize prediction of treatment response using biomarkers measured at baseline across modalities. In the first strategy, we will combine the specific biomarker-candidates across all modalities (as predefined in **Appendix 1**), which will generate around 50 candidate biomarkers. A dimension reduction step will be used to define a small number of predictors (roughly 5–10) that will be used in a logistic regression model. The second strategy will use an algorithm to (i) identify, in a data-driven way, biomarkers with a predictive value among all the existing biomarkers (roughly 5,000–10,000) and (ii) predict treatment response based on the identified subset of informative biomarkers. We will investigate the use of machine learning methods (e.g., random forest, neural networks) as well as ensemble methods [e.g., Super Learner (116)]. The assessment of the predictive performance of these strategies will be carried out as described in the previous section.

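### The AUC of a clinical-plus-biomarker model is reported as the biomarker's own performance, with no stated clinical-only reference

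*Protocol article*

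**What the plan says.** In *Evaluation of the Predictive Value of the Biomarkers Within Modality*, each patient's probability of being a remitter rather than a non-responder comes from a logistic model, "based on its clinical data and the value of a modality-specific biomarker". The ROC curve is built from those probabilities, and "we will focus on the ROC curve with high-specificity". The AUC over that part of the curve "will be reported as a summary of the predictive performance of each biomarker". Accuracy and positive and negative predictive values at a chosen threshold come from the same model, and "these measures will be estimated using five-fold cross-validation". On testing, the section says: "A permutation procedure will be used to obtain the null distribution of the predictive performance, against which the observed performance will be compared". It names neither a model with the clinical data alone nor an increment over one, and it does not say whether outcomes or biomarker values are permuted.

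The next section, *Predictive Value of the Biomarkers Across Modalities*, adopts the same approach: "The assessment of the predictive performance of these strategies will be carried out as described in the previous section".

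The separate association analyses do adjust for other variables: "Regression models will be adjusted for age and sex, as well as modality-specific relevant covariates".

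**The concern.** The ROC curve describes a model with two sources of information, the clinical data and the biomarker. Its area is then attributed to one of them. If the clinical data carry any prognostic information, the area exceeds what the biomarker earned, and without a clinical-only figure the reader cannot see by how much.

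The test may share the problem. Permuting the outcome gives a null in which neither the clinical data nor the biomarker predicts. Rejecting that null shows that something in the model predicts, not that the biomarker does.

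Identifying biomarkers of response is the stated main purpose of the trial. Since the within-modality models all contain clinical data, one prognostic clinical variable could lift the reported AUC for PET, EEG, fMRI, cognition and blood markers together. That could be mistaken for convergent evidence.

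**Working it through.** **Plan's own figure.** The section gives no AUC target, significance level or clinical AUC, so there is nothing to reproduce. The question is what a useless biomarker would score under the plan.

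**Inputs from the article.** Logistic model, five-fold cross-validation, high-specificity part of the ROC curve. With 100 patients and 20% drop-out, 100 × 0.80 = 80 are evaluable. A remission rate of about 50% (*Materials and Methods*) gives 40 remitters; the 33% in the prediction section gives about 26.

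**Assumptions not in the article.**
- Nominal level 5%.
- High specificity taken as at least 0.80.
- Clinical data with true AUC between 0.50 and 0.75.
- 20 non-responders. This is the number at which the PET inputs give about the stated power ("We estimated that we needed to include 100 patients to reach a statistical power of 80" per cent). The difference is 0.08 × 0.71 = 0.0568, and 0.0568 / 0.073 = 0.778 SD. Then 0.778 / √(1/40 + 1/20) = 2.84, and Φ(2.84 − 1.96) ≈ 0.81.
- 40 vs 40 and 26 vs 20 are shown as alternatives.

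**Simulation.** 600 trials per scenario and 199 permutations. Predictors were age and sex (both uninformative), one prognostic clinical variable and a biomarker of pure noise. The clinical variable differs between groups by d = √2 · Φ⁻¹(AUC); for AUC 0.70, d = 1.414 × 0.524 = 0.74. The p-value is (1 + number of permuted values at or above the observed one) / 200. Two nulls were compared: (A) outcome permuted against all predictors; (B) only the biomarker permuted.

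**Results.** The last four columns give the percentage of trials in which the noise biomarker is declared predictive.

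| Remitters vs non-responders | Clinical AUC | CV AUC, clinical only | CV AUC, clinical + noise | A: full AUC | A: partial AUC | B: full AUC | B: partial AUC |
|---|---|---|---|---|---|---|---|
| 40 vs 20 | 0.50 | 0.484 | 0.489 | 5.5 | 4.8 | 5.2 | 5.5 |
| 40 vs 20 | 0.60 | 0.545 | 0.540 | 13.5 | 10.3 | 5.3 | 4.3 |
| 40 vs 20 | 0.65 | 0.591 | 0.582 | 25.8 | 21.2 | 5.7 | 4.2 |
| 40 vs 20 | 0.70 | 0.648 | 0.639 | 47.5 | 37.7 | 4.3 | 6.5 |
| 40 vs 20 | 0.75 | 0.704 | 0.693 | 67.5 | 52.7 | 4.8 | 4.2 |
| 40 vs 40 | 0.60 | 0.546 | 0.542 | 16.2 | 13.0 | 4.8 | 4.8 |
| 40 vs 40 | 0.70 | 0.667 | 0.658 | 68.3 | 52.3 | 3.8 | 3.3 |
| 40 vs 40 | 0.75 | 0.721 | 0.714 | 89.8 | 77.5 | 5.8 | 5.2 |
| 26 vs 20 | 0.60 | 0.523 | 0.520 | 10.7 | 9.0 | 4.8 | 4.8 |
| 26 vs 20 | 0.65 | 0.583 | 0.577 | 19.8 | 17.7 | 5.2 | 4.8 |

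The Monte Carlo standard error at 5% is √(0.05 × 0.95 / 600) = 0.9 percentage points.

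**Reading the table.**
1. The AUC that the plan would attribute to the noise biomarker is that of the clinical-only model to within about 0.01. For 40 vs 20 at clinical AUC 0.70, 0.639 − 0.648 = −0.009. The biomarker's true contribution is nil, yet the reported value is 0.64. Cross-validation does not help: it removes optimism from overfitting, not the clinical signal.
2. Under scheme A the false-positive rate rises with the clinical AUC. Under scheme B it stays between 3.3% and 6.5%.
3. A separate simulation with 27 vs 27 patients, two clinical variables, 250 trials and 99 permutations agrees. Scheme A declares the noise biomarker predictive in 26%, 50% and 72% of trials at clinical AUC 0.64, 0.70 and 0.75; scheme B in 3% to 6%.

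**The case against.** The strongest defence has five parts.

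- **The permutation scheme is not stated.** A reader might infer that the null is that nothing predicts. The wording suggests this, since it speaks of the performance as a whole, but the article does not say it. Such detail may sit in a fuller document. If only the biomarker is permuted, the test is valid. This stands, so the false-positive rates are conditional. The AUC label is wrong under either scheme.
- **A clinical-only model may be fitted anyway.** The association section lists clinical and demographic profiles among the modalities of interest, and performance is to be evaluated modality by modality. That makes such a model plausible. It is nowhere named as the reference for the other modalities, and no difference is to be reported.
- **Other analyses isolate the biomarker.** The primary regressions adjust for age, sex and modality-specific covariates, and the PET latent variable model gives a single test. This stands: they are unaffected, and a noise biomarker would be expected to show nothing there. They test association, however, and do not correct a misattributed AUC.
- **The size depends on assumed clinical AUCs.** This stands. At clinical AUC 0.60 the full-AUC rate under outcome permutation is 10.7% to 16.2% across the three splits, and with uninformative clinical data it is near nominal. A reader might infer that every modality would pass; none of the simulated rates reaches 100%, and the article gives no clinical AUC.
- **The cross-modality section does not say that clinical data enter its models.** This stands. A reader might infer that both strategies are affected, but the text supports this only where clinical data are among the predictors.

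**Conclusion.** The point holds in two parts of different strength.

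**Unconditional on the permutation scheme:** the article reports a combined model's cross-validated (partial) AUC as the biomarker's performance and states no clinical-only reference, so any clinical contribution is credited to the biomarker. With 40 vs 20 patients and clinical AUC from 0.60 to 0.75, a noise biomarker is credited with a mean AUC of about 0.54 to 0.69. The excess vanishes only if the clinical data are uninformative. The accuracy and predictive values from the same model carry the same misattribution.

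**Conditional:** if the outcome is permuted, the noise biomarker is declared predictive in about 10% to 53% of trials on the partial AUC and 14% to 68% on the full AUC over that range, against a nominal 5%. The partial AUC is the plan's own summary, so the first range is the more relevant.

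These sizes rest on the assumed group sizes, significance level, specificity cut-off and clinical AUCs, and on a simulated biomarker independent of the clinical data.

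**What to change.** In the within-modality section:

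1. List the variables that make up the clinical data and fit the clinical-only model in the same five folds.
2. Report the cross-validated (partial) AUC of the clinical-only model, of the clinical-plus-biomarker model, and their difference. Call the difference, not the combined AUC, the biomarker's predictive value.
3. State what is permuted. Base the p-value on permuting the biomarker, or the block of biomarkers, while each patient's outcome and clinical data stay together.
4. Do the same in the cross-modality strategies where clinical data enter the model, and state whether they do.

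This needs no new data, only some plan text and a little extra analysis code. The price is that headline values become less favourable: a biomarker that adds nothing will show a difference near zero instead of a respectable AUC.

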
##### Clinical Response Status

###### Primary Clinical Outcome Measure

The primary outcome measure is categorical and built to capture patients with an early as well as sustained, either excellent or poor response to treatment. Patients are classified as either “remitters”, “non-responders”, or “intermediate responders” after 8 weeks of treatment. These categories are based on percentage changes of depressive symptoms from baseline, as measured by HAMD_6_. Remitters must have ≥50% reduction in HAMD_6_ at 4 weeks (early responders) and a HAMD_6_ score <5 after 8 weeks of treatment. Non-responders have <25% reduction in HAMD_6_ after 4 weeks (early non-responder) and <50% reduction in HAMD_6_ after 8 weeks of treatment. Patients who do not meet the criteria above are defined as “intermediate responders” at week 8. The primary predictor analyses are directed to predict treatment response in a binary fashion (either remitter or non-responder (see **Figure 3**).

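### Accuracy, PPV and NPV are planned for remitters versus non-responders only, so they describe the extreme groups and not all patients starting treatment

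*Protocol article*

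**What the plan says.** Under Primary Clinical Outcome Measure the protocol article defines three classes. Both the week-4 and the week-8 score enter the definition; for example, "Remitters must have ≥50% reduction in HAMD_6_ at 4 weeks (early responders) and a HAMD_6_ score <5 after 8 weeks of treatment". Patients who fit neither extreme are intermediate responders. The same section then narrows the target: "The primary predictor analyses are directed to predict treatment response in a binary fashion", meaning remitter or non-responder.

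The section on predictive value within modality follows this. Logistic regression gives "the probability of each patient to be a remitter (vs. a non-responder"), and the decision rule is that "patients with an estimated probability greater than the threshold will be predicted to be remitters, otherwise to be non-responders". The summary measures include "The classification performance (accuracy, positive predictive value, negative predictive value") and the AUC over the high-specificity part of the ROC curve. The reason given for that focus begins "Since a 33% remission rate is expected in treatment regimen comparable to ours (5"). The section on prediction across modalities assesses the multimodal and machine-learning predictors in the same way.

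Two other analyses can include intermediate responders. One is the secondary regression on relative change in HAMD6, which is a test of association. The other is a set of additional classification schemes, such as at least 50% reduction at week 8, which the article says may be considered.

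**The concern.** Contrasting the extremes is a sound way to test a mean difference. PPV, NPV and accuracy are different, because they depend on the mix of patients who are scored. A model of remitter against non-responder, scored on those two labels, has no place for intermediate responders. At baseline, when a predictor would be used, nobody knows who will turn out intermediate. The Discussion says the trial concerns response to standard treatment under naturalistic conditions, which means everyone who starts.

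A reader who takes the reported PPV as the chance that a marker-positive patient will remit would therefore be misled. Cross-validation and the permutation test guard against overfitting and chance; neither corrects this selection. The predictive values also depend on the remission rate. The article uses about 50% in the sample-size paragraph of Materials and Methods and 33% in the prediction section.

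**Working it through.** **1. What can be reproduced.** The article gives no expected predictive performance. Its only related figure is the sample size: "include 100 patients to reach a statistical power of 80"%. Inputs from Materials and Methods are a difference of 8% of 0.71 = 0.0568 and an SD of 0.073, so d = 0.0568/0.073 = 0.778. A 20% drop-out leaves 80 patients, and 50% remission gives 40 remitters. With an assumed two-sided 5% test, power = Φ(d/√(1/n₁ + 1/n₂) − 1.96).
- 40 v 40: Φ(3.48 − 1.96) = 0.94
- 40 v 20: Φ(2.84 − 1.96) = 0.81

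The stated 80% returns if about 20 of the 80 (25%) are intermediate. That is only an inference. A stricter significance level would also bring the size near 100: at 0.01, 39 per group, or 98 after drop-out.

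**2. Formulas.** Let r, n and f be the shares of remitters, non-responders and intermediates (r + n + f = 1), Se and Sp the sensitivity and specificity in the extremes, and q the share of intermediates called remitter.
- Two groups, as planned: PPV = rSe/[rSe + n(1−Sp)]; NPV = nSp/[nSp + r(1−Se)]; accuracy = (rSe + nSp)/(r + n).
- All patients, plan's two labels: each intermediate is misclassified. The PPV denominator gains fq and the NPV denominator gains f(1−q), with numerators unchanged, so neither can rise. Accuracy = rSe + nSp, which is (1−f) times the planned accuracy.
- All patients, remitter versus all others: PPV is the same as under the plan's labels. NPV gains f(1−q) in both numerator and denominator, so it cannot fall. Accuracy = rSe + nSp + f(1−q).

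**3. Illustration** (assumed: r = 0.33, Se = Sp = 0.70, q = 0.5).

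| | n = 0.33, f = 0.34 | n = 0.20, f = 0.47 |
|---|---|---|
| PPV, two groups | 0.231/(0.231+0.099) = 0.70 | 0.231/(0.231+0.060) = 0.79 |
| PPV, all patients | 0.231/(0.330+0.170) = 0.46 | 0.231/(0.291+0.235) = 0.44 |
| NPV, two groups | 0.231/(0.231+0.099) = 0.70 | 0.140/(0.140+0.099) = 0.59 |
| NPV, all, plan's labels | 0.231/(0.330+0.170) = 0.46 | 0.140/(0.239+0.235) = 0.30 |
| NPV, all, remitter v others | 0.401/0.500 = 0.80 | 0.375/0.474 = 0.79 |
| Accuracy, two groups | 0.462/0.66 = 0.70 | 0.371/0.53 = 0.70 |
| Accuracy, all, plan's labels | 0.46 | 0.37 |
| Accuracy, all, remitter v others | 0.231+0.401 = 0.63 | 0.231+0.375 = 0.61 |

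The remitter share within the extremes is 33/66 = 50% or 33/53 = 62%. Both rest on the assumed non-responder shares.

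**4. Same check with the plan's own effect size.** Take d = 0.778, normal distributions, a cut that maximises sensitivity plus specificity (Se = Sp = Φ(0.389) = 0.65) and intermediates halfway between the extremes. The remission rates are the article's; the intermediate share of 26% is assumed.

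| r / f / n | Two groups: accuracy, PPV, NPV | All, plan's labels | All, remitter v others |
|---|---|---|---|
| 50 / 26 / 24% | 0.65, 0.80, 0.47 | 0.48, 0.60, 0.34 | 0.61, 0.60, 0.62 |
| 33 / 26 / 41% | 0.65, 0.60, 0.70 | 0.48, 0.44, 0.52 | 0.61, 0.44, 0.78 |

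At 50% remission, with f at 15%, 26% and 40%:
- accuracy under the plan's labels is 0.65 × (1−f) = 0.55, 0.48 and 0.39;
- PPV goes from 0.73 to 0.62, 0.80 to 0.60 and 0.90 to 0.58;
- the full AUC for remitter versus others is 0.68, 0.66 and 0.63, against 0.71 in the extremes.

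The AUC would not fall if intermediates looked just like non-responders on the marker. The plan reports a partial AUC, so the full AUC shows direction only.

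**The case against.** The extreme-group contrast is declared openly, and it is a legitimate target at the discovery stage. The trial does not ignore intermediate responders: the secondary continuous analysis covers the full range of outcomes, and the 50% response scheme would classify everyone. The article never says that intermediates are deleted; their absence follows from the two-class model. It claims potential biomarkers and hopes to pave the way for precision medicine, not to deliver a validated tool. It would therefore be too strong to say that the results cannot serve that aim.

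Much of this stands, and it limits the point to labelling and a companion analysis. It does not remove the point. The continuous analysis yields no predictive values, and the 50% response scheme is optional and concerns a different outcome.

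A reader might also infer that all three measures are overstated for all patients. The documents do not support that. The direction for NPV depends on the target: it falls if a negative result is read as non-responder, and rises if it is read as not a remitter. Nor is a 50–62% remitter share among the extremes a figure from the plan.

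**Conclusion.** The point holds in a limited form: the planned accuracy, PPV and NPV describe remitters and non-responders, not all patients starting treatment.

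Three directions follow from algebra alone. PPV for remission is overstated whenever any intermediate is called a remitter. Under the plan's own labels, accuracy shrinks by one minus the intermediate share, and NPV cannot rise. For remitter versus all others, NPV cannot fall.

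The sizes are assumptions, because the article gives neither the intermediate nor the non-responder share. Across the cases worked, the loss in PPV runs from 0.11 (0.73 to 0.62) to 0.35 (0.79 to 0.44). Accuracy for remitter versus all others falls less than under the plan's labels.

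The two remission rates should be reconciled. Whether either uses this trial's two-timepoint HAMD6 definition cannot be checked from the article.

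**What to change.** - Keep the extreme-group contrast for the association test and as the declared primary classifier. Label its accuracy, PPV, NPV and AUC as applying to the extreme groups only.
- Make an all-patient report required rather than optional. Assign intermediate responders to the cross-validation folds, score them with the model fitted to remitters and non-responders in the other folds, and give PPV, NPV, accuracy and AUC over all patients with a verified week-8 outcome, at the observed class rates.
- Name the target each time: remitter versus all others, and non-responder versus all others. Do this for single-modality and combined predictors.
- Report the observed share of each class, and state which remission rate applies to which population.

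Replacing the primary contrast is not needed; that would be a trade-off against the declared design. The change uses data the trial already collects. It costs a little more analysis and a lower headline PPV, while NPV for remission may come out higher.

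### The cut-off rule for accuracy, PPV and NPV omits sensitivity, so it fixes no threshold as printed; the place of threshold selection in the cross-validation should also be stated (minor)

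*Protocol article*

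**What the plan says.** All but the last of these statements are in the protocol article, section Evaluation of the Predictive Value of the Biomarkers Within Modality.

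- **Classification rule:** a logistic model gives each patient a probability of remission, and "patients with an estimated probability greater than the threshold will be predicted to be remitters, otherwise to be non-responders".
- **Purpose of the ROC curve:** it "will be used to assess the compromise between sensitivity and specificity of this classification across thresholds".
- **Region of interest:** "Since a 33% remission rate is expected in treatment regimen comparable to ours (5), we will focus on the ROC curve with high-specificity". No numerical bound is given for high specificity.
- **Main summary:** "The AUC (area under the curve) of the relevant part of the ROC curve will be reported as a summary of the predictive performance".
- **Threshold-based measures:** accuracy, PPV and NPV "at the threshold optimizing the sum specificity and specificity will also be reported".
- **Protection against optimism:** "To limit optimistic biases, these measures will be estimated using five-fold cross-validation". A permutation null distribution for predictive performance follows.
- **Reach:** the next section, Predictive Value of the Biomarkers Across Modalities, carries the method over to the combined models: "The assessment of the predictive performance of these strategies will be carried out as described in the previous section".

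**The concern.** The rule sums specificity with itself, and the article states it correctly nowhere else. Taken literally, it rewards only the avoidance of false remitter calls, which can always be achieved by raising the cut-off. It therefore cannot select an operating point.

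Two further questions arise once the rule is read as intended. The first is whether an equally weighted criterion sits in the region that the section declares relevant. The second is whether the cut-off is chosen on the same predictions that are then scored. Cross-validating the model does not remove optimism from a cut-off tuned afterwards on the held-out predictions.

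At stake are the accuracy, PPV and NPV reported for each biomarker and for the combined models. These are the figures a clinical reader is most likely to carry away from a prediction study.

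**Working it through.** The plan gives no numerical result for this rule, so there is no figure to reproduce first. Three checks follow.

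**1. The rule as printed.** A patient is called a remitter if the probability p exceeds the cut-off t. Then

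- specificity(t) = share of non-responders with p ≤ t, which never falls as t rises;
- specificity + specificity = 2 × specificity(t) ≤ 2, with equality for every t at or above the highest p among non-responders.

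The maximum is thus a whole range of cut-offs. It includes the cut-off above all patients (no predicted remitters, sensitivity 0, PPV undefined). It can also include cut-offs that still pick up some remitters. To see how often, 5,000 trials of 80 patients were simulated at the planning effect derived in check 2. Some cut-off with specificity 1 still identified at least one remitter in 76% of trials with 26 remitters v 54 non-responders, and in 89% with 40 v 40. The mean best sensitivity there was 0.08 and 0.10.

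**2. The rule as evidently intended (sensitivity + specificity).** The inputs come from the power statement in Materials and Methods: an 8% difference, mean BP_ND 0.71, SD 0.073.

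- Difference = 0.08 × 0.71 = 0.0568.
- d = 0.0568 / 0.073 = 0.778.
- For a normal marker with equal variances (an assumption), AUC = Φ(d/√2) = 0.709.
- The Youden cut-off lies midway between the group means, so sensitivity = specificity = Φ(d/2) = Φ(0.389) = 0.651.

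At the section's 33% remission rate:

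- PPV = 0.651 × 0.33 / (0.651 × 0.33 + 0.349 × 0.67) = 0.48.
- NPV = 0.651 × 0.67 / (0.651 × 0.67 + 0.349 × 0.33) = 0.79.

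For comparison, specificity 0.90 (an illustrative value) gives sensitivity 0.31, PPV 0.60 and NPV 0.73. For d from 0.5 to 1.5, the Youden specificity runs from 0.60 to 0.77. In the same 5,000 simulated trials, the specificity chosen in the sample had a median of 0.68 to 0.69. It was below 0.80 in 77 to 78% of trials and below 0.90 in about 94%.

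**3. Where the cut-off is chosen.** An uninformative marker was simulated in 2,000 trials per setting, with a one-predictor logistic model, stratified five-fold cross-validation and the sensitivity + specificity rule. The group sizes are assumptions. The article does not give the numbers of remitters and non-responders to be analysed.

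| Remitters v non-responders | Base rate | Balanced accuracy, cut-off tuned on pooled held-out predictions | PPV, same | Balanced accuracy, cut-off from training folds | PPV, same |
|---|---|---|---|---|---|
| 27 v 27 | 0.50 | 0.57 | 0.60 | 0.50 | 0.50 |
| 26 v 16 | 0.62 | 0.58 | 0.74 | 0.50 | 0.62 |
| 40 v 40 | 0.50 | 0.56 | 0.59 | 0.50 | 0.50 |

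The 90th percentiles of balanced accuracy under pooled tuning were 0.65, 0.67 and 0.63. The excess in PPV over the base rate is about 0.10, 0.12 and 0.09. Selection inside the training folds removes it.

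**The case against.** The strongest reply is that this is a slip of one word. The same section says that the ROC curve weighs sensitivity against specificity, and no analyst would add specificity to itself. That stands as to intent, and it is why the point is minor. It does not make the printed rule usable.

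Three stronger readings are tempting, and the document does not support them.

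- **That the printed rule predicts no remitters, with PPV undefined.** This is only one of many tied optima, as check 1 shows.
- **That the intended rule contradicts the high-specificity focus.** The focus is carried by the partial AUC, and the threshold-based measures are reported in addition. Two summaries of one curve can coexist. The Youden point is merely not aligned with the declared region, and replacing it by a minimum-specificity rule would be a preference.
- **That the plan tunes the cut-off on the predictions it scores.** The text does not say so. It says that these measures are estimated by five-fold cross-validation, and selection inside the training folds is a natural reading. An article may leave that detail to the full protocol or SAP.

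The permutation procedure is also a real safeguard. If each permutation repeats the cut-off search, the null distribution carries the same optimism and the p-value is protected. The reported accuracy, PPV and NPV would still not be corrected.

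**Conclusion.** The point holds in a limited form. The threshold rule is wrong as printed and identifies no unique cut-off, and the error extends to the combined models by cross-reference. Read as sensitivity plus specificity, it is a legitimate additional summary. Its operating point would be near specificity 0.65 at the planning effect, given an equal-variance normal marker, so readers should not take it as describing the high-specificity region.

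The optimism is conditional. It amounts to about 0.06 to 0.08 in balanced accuracy and 0.09 to 0.12 in PPV for a marker with no information, and it arises only if one cut-off is tuned on the pooled held-out predictions. The figures rest on the assumed group sizes and a single-predictor model.

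Severity is minor. The regression and latent variable tests and the partial AUC do not depend on this cut-off.

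**What to change.** Replace the criterion with: the threshold maximising the sum of sensitivity and specificity, chosen in the training folds and applied unchanged to the held-out fold. Add that the threshold selection is repeated in each permutation. Optionally, also report accuracy, PPV and NPV at the specificity that bounds the partial AUC, with that value stated in advance, so that one set of figures describes the declared region.

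The cost is a sentence or two and a small change to the code. If pooled tuning had been intended, the reported performance will be slightly lower, because the optimism is removed.
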